### Interventions

2.5

This study will select patients who meet the criteria of this study by recruiting in the hospital. A randomized controlled study will be used, in which the control group: conventional treatment; the experimental group: Tai Chi exercise will be added to the control group. The 2 groups of patients will receive the same routine care. During the trial period, avoid smoking, alcohol and irritating food, avoid strenuous exercise, and pay attention to adverse reactions. When necessary, the attending doctor can appropriately adjust the plan according to the patient's condition, and all intervention methods will be recorded in detail for the final result analysis. Efficacy assessors are not aware of the study group plan, and data statisticians are not involved in the design and implementation of the study. Before and after treatment, the health status of each patient will be evaluated, including the outcome indicators, and all patients will be followed up by telephone. Follow-up content includes cardiovascular events and rehospitalization.

Control group: according to the relevant guidelines after myocardial infarction intervention, standard drug treatments will be given, including antiplatelet drugs, statins, angiotensin converting enzyme inhibitors, nitrates, β-receptor blockers, and health education. The content of the education includes the control of myocardial infarction risk factors, techniques for improving sleep quality, diet guidance, etc, and pays attention to communicating with patients, mastering their psychological and emotional changes, and avoiding or alleviating bad moods such as anxiety and depression in elderly patients.

Experimental group: on the basis of conventional treatment, the experimental group will be given 24 simplified Tai Chi. Professional Tai Chi teachers will teach and practice the subjects to ensure that the practice time and movement rhythm are basically the same. The whole set of Tai Chi includes 3 parts: preparation activity, training activity and end activity, totaling about 20 minutes, twice a day, once in the morning and once in the afternoon, and lasts for 24 weeks.

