## Introduction

1

With the change in lifestyles, hypertension, hyperglycemia, hyperlipidemia, smoking, lack of exercise, aging of population, and other risk factors, the incidence of coronary heart disease is increasing year by year, and it has become 1 of the main diseases that affect global health.^[1]^ Myocardial infarction is 1 of the cardiovascular diseases with the highest mortality,^[2]^ and it is a serious threat to people's life and health.^[3]^ Early intervention and standardized drug treatment has greatly reduced the mortality of patients with myocardial infarction, but there is a lack of attention to rehabilitation after the onset of disease. Most patients with myocardial infarction fear exercise, resulting in decreased activity tolerance, decreased cardiopulmonary function, anxiety, decreased quality of life, relapsed illness, and often require hospitalization, which brings a heavy burden to the patient's family and society.^[4]^ Therefore, there is an urgent need to find a method that is simple and easy to operate, with less side effects, that can improve patients’ cardiac function and exercise tolerance, thereby improving the quality of life.

Tai Chi, originated in ancient China, is mainly divided into 5 schools: Chen, Yang, Wu, Wu, and Sun. It is divided into 24 styles, 36 styles, and 108 styles. It is a medium-strength defensive exercise,^[5]^ with the characteristics of health care, economy and convenience.^[6,7]^ Studies have found that Tai Chi exercise can increase patient endurance, balance and sensitivity, and improve the quality of life of patients.^[8,9]^ At the same time, moderate-intensity aerobic exercise is the core content of cardiac rehabilitation, which can not only enhance the relative adaptability of heart function, but also improve the blood supply capacity of the coronary artery of the heart to a certain extent, and reduce the cardiovascular mortality rate by 20% to 30%.^[10]^ As an ancient exercise training, Tai Chi has the characteristics of ease and softness, smoothness and unobstructed intention, which is convenient for patients’ participation and persistence. It has advantages for the rehabilitation of patients with myocardial infarction, but there is currently a lack of large sample comparisons in the academic community.

Therefore, we plan to evaluate the efficacy and safety of Tai Chi on the cardiac function of patients with myocardial infarction through this randomized controlled trial.

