### Patients

2.3

Diagnostic criteria: ① Diagnosis of myocardial infarction in the fourth edition of the General Definition of Myocardial infarction in the European Society of Cardiology 2018^[11]^; ② According to the New York Heart Association (NYHA) cardiac function classification standard, cardiac function is grade I to III.

Inclusion criteria: ① Meet the diagnostic criteria for myocardial infarction; ② Age ≥35 years old and ≤80 years old; ③ Cardiac function grade I to III; ④ Stable condition after interventional surgery without serious complications; ⑤ Have a certain communication and understanding ability, express their wishes correctly; ⑥ After informed consent and signed an informed consent form, they voluntarily participated in this research project.

Exclusion criteria: (A standard for judging whether a patient can become a experimental object): ① Suffer from acute systemic disease; ② Cardiac function grade IV; ③ Risk stratification of cardiac rehabilitation in patients with coronary heart disease^[12]^ showed that they are at high-risk; ④ Relative or absolute contraindications for rehabilitation exercise such as blood pressure drop during exercise; ⑤ Limb dysfunction; ⑥ Complicated with severe mental illness; ⑦ Unable to understand the research plan after explanation or unwilling to participate.

Exclusion criteria: (A criterion used to screen patients who have become experimental subjects, but the relevant data cannot be included in the final data analysis): ① Severe adverse events or serious complications are not suitable for the next test; ② Poor compliance, which affects the judgment of efficacy and safety; ③ The disease progresses during the treatment process, and the treatment plan needs to be changed; ④ For any reason, the subject asked to withdraw from the trial.

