#### Efficacy indicators

2.6.1

Main efficacy indicators: total effective rate: referring to the “Guiding Principles for Clinical Research of New Chinese Medicines”,^[13]^ total effective rate = (marked effective number + effective number)/total number × 100%. According to NYHA grading method, evaluate the curative effect of cardiac function: ① Marked effective: cardiac function improved by more than grade 2; ② Effective: cardiac function improved by grade 1, but not as good as grade 2; ③ Ineffective: cardiac function improved less than grade 1; ④ Deterioration: the deterioration of heart function is less than grade 1.

Secondary efficacy indicators: 6 minutes walking test, brain natriuretic peptide, left ventricular ejection fraction, medical outcomes study short-form36 (SF-36).

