#### Adverse reaction rate

2.6.2

Including any uncomfortable symptoms (such as dizziness, nausea, etc) during treatment.

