### Sample collection

2.7

Data will be collected according to the evaluation criteria before the start of treatment, 12 weeks after the treatment, and at the end of 24 weeks of treatment. After the treatment, each patient will be followed up by telephone for 3 months. Detailed follow-up information can not be collected and the reasons for loss to follow-up will be recorded. Access to the database is limited to the researchers of this research group.

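### Cardiovascular events and rehospitalisation after treatment belong to no outcome, and a removal rule for severe adverse events conflicts with the analysis sets, so the safety comparison could leave out the most serious events

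*Protocol article*

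**What the plan says.** The Introduction gives the aim: "we plan to evaluate the efficacy and safety of Tai Chi on the cardiac function of patients with myocardial infarction".

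Section 2.5 (Interventions) describes telephone follow-up of all patients: "Follow-up content includes cardiovascular events and rehospitalization". Section 2.7 (Sample collection) gives its timing: "After the treatment, each patient will be followed up by telephone for 3 months".

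Section 2.6 lists the outcomes. The primary is the total effective rate, based on change in NYHA grade. The secondary outcomes are the walking test, natriuretic peptide, ejection fraction and SF-36. The safety measure, in 2.6.2, is an adverse reaction rate: "Including any uncomfortable symptoms (such as dizziness, nausea, etc) during treatment".

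Three other places bear on safety:
- Section 2.3 (Patients) has a second exclusion list for patients already in the trial, whose data are to be kept out of the final analysis. Its first item reads: "Severe adverse events or serious complications are not suitable for the next test".
- Section 2.8 monitors every participant throughout, sends all adverse events to the ethics committee for review and a ruling on causality, and sets up a safety board.
- Section 2.9 defines an intention-to-treat full analysis set, a per-protocol set and a safety set, and compares the incidence of adverse events by chi-square test.

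**The concern.** After an infarction, the events that matter most for the safety of an exercise programme are new cardiovascular events, readmission and death. The protocol plans to ask about the first two but does not make them part of any result it commits to report. The safety measure it does define is illustrated by mild symptoms and ends with treatment.

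The rule in 2.3 adds to this. If it is followed literally, a patient with a severe event leaves the analysis together with the event. The arm with more serious events would then lose more of them from the comparison. A safety conclusion drawn from what remains could look favourable even if reinfarction or readmission differed between the arms.

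**Working it through.** **1. Where each kind of event goes.**

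| Event | Collected or reviewed | Listed outcome (2.6) | Analysis (2.9) | Removal list (2.3) |
|---|---|---|---|---|
| Mild symptom on treatment | Yes | Yes, 2.6.2 | Chi-square | Not affected |
| Serious event on treatment | Yes, 2.8 | Not named | Could count as an adverse event | Data barred from final analysis |
| Cardiovascular event or readmission in the 3 months after treatment | Yes, 2.5 and 2.7 | None; 2.6.2 ends with treatment | Not named | Unclear |

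Row 2 contains a contradiction. Section 2.3 removes these patients' data, while neither the full analysis set nor the safety set in 2.9 drops a patient for a severe adverse event. The document does not say which rule prevails. Row 3 is a gap: the data are collected but assigned to no outcome.

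The terms also differ. Section 2.6.2 defines an adverse *reaction* rate, while 2.8 and 2.9 speak of adverse *events*, and the article does not say whether these are the same.

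**2. The plan's own sample size.** Inputs from section 2.4: π = 0.8, δ = 0.15, c = 1, normal quantiles 1.64 and 1.28.

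n = 0.8 × 0.2 × [(1.64 + 1.28)/0.15]² × 2 = 121.26, rounded up to 122 per group. With 10% dropout, 122/0.9 = 135.6, so 136 per group and 272 in total. Both stated figures are reproduced. They concern the effective rate, and nothing proposed here changes them.

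**3. What an event comparison could show.** The protocol gives no event rate, so the rates below are assumptions. With the same rate p in both arms, the 95% half-width for a risk difference is 1.96 × √[2p(1 − p)/n].

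| Assumed p | n = 136 per arm | n = 122 per arm |
|---|---|---|
| 5% | 1.96 × √(0.095/136) = 5.2 points | 1.96 × √(0.095/122) = 5.5 points |
| 10% | 1.96 × √(0.18/136) = 7.1 points | 1.96 × √(0.18/122) = 7.5 points |

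Power to detect a doubling of the control rate, with 136 per arm and a two-sided 5% test, is about 22% at a control rate of 3%, 35% at 5%, 64% at 10% and 85% at 15%. At rates of 3% to 10% the comparison would be mainly descriptive: it could bound a large harm but not exclude a moderate one.

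**The case against.** The strongest reply is that serious events are not ignored. Section 2.8 covers all participants and all adverse events, and 2.9 tests adverse-event incidence and gives a chi-square test for counts generally. The wording of 2.6.2 is open-ended, and a reinfarction on treatment would naturally be recorded as an adverse event. The safety set does not drop patients for severe events. A full protocol or analysis plan may also hold the event definitions and safety tables, and their absence from a journal article is no fault.

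Much of this stands, and it limits the point. A reader might infer that serious events get no between-arm comparison at all; the adverse-event test in 2.9 does not support that. A reader might infer that controls are seen only at weeks 12 and 24 and so report fewer symptoms. But both groups receive the same routine care, controls also receive health education, every participant is monitored, and nothing says the Tai Chi teachers collect symptoms. Nor does the abstract make fewer cardiac recurrences a goal of this trial: it mentions them as background, and the aim it states is cardiac function.

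The reply does not remove the conflict between 2.3 and 2.9, which is in the text and not a matter of missing detail. Review by an ethics committee or safety board is oversight and does not commit the trial to a comparison by arm. And 2.6 sets out the outcomes without giving the telephone-reported events a place.

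**Conclusion.** The point holds in a limited form. On-treatment serious events could be counted under 2.9, but 2.3 as written takes the data of the affected patients out of the final analysis. Events in the 3 months after treatment are collected without belonging to any outcome. The between-arm safety comparison could therefore leave out the most serious events. The documents do not establish that it will, because they do not say which of 2.3 and 2.9 governs.

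No stated figure is wrong, and the sample size is unaffected. The size of any bias cannot be computed, since no event rates are given; the half-widths and power above rest on assumed rates. This should be corrected before analysis, because the protocol claims safety as an aim and plans to collect the data needed to address it.

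**What to change.** - In 2.6.2, name a safety outcome: any cardiovascular event, rehospitalisation or death, from randomisation to the end of the 3-month telephone follow-up.
- State that the second exclusion list in 2.3 does not apply to this outcome, and reconcile that list with the analysis sets in 2.9.
- Analyse all randomised patients in their assigned arm, including those who stop the programme. The safety set alone is not enough, because it requires a safety visit after medication and so omits anyone whose event comes before that visit and prevents it.
- Ask the same scripted question in both arms at week 12, week 24 and by telephone.
- Report counts by arm and a risk difference with its 95% confidence interval, as descriptive, with no efficacy claim.
- Say how the adverse reactions of 2.6.2 relate to the adverse events of 2.8 and 2.9, and use one term.

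The cost is one outcome line, one table and one scripted question at contacts already planned, with no new patients or visits. The downside is an interval of about ±5 to ±7.5 points at the assumed rates, which must be reported as it is and not read as evidence of no difference.

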### Outcomes

2.6

#### Efficacy indicators

2.6.1

Main efficacy indicators: total effective rate: referring to the “Guiding Principles for Clinical Research of New Chinese Medicines”,^[13]^ total effective rate = (marked effective number + effective number)/total number × 100%. According to NYHA grading method, evaluate the curative effect of cardiac function: ① Marked effective: cardiac function improved by more than grade 2; ② Effective: cardiac function improved by grade 1, but not as good as grade 2; ③ Ineffective: cardiac function improved less than grade 1; ④ Deterioration: the deterioration of heart function is less than grade 1.

Secondary efficacy indicators: 6 minutes walking test, brain natriuretic peptide, left ventricular ejection fraction, medical outcomes study short-form36 (SF-36).

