### Sample size

2.4

According to the calculation formula:

$${\text{n}}_{1}=\pi (1-\pi ){\left[\frac{\left(\mu_{1-\alpha }+\mu_{1-\beta }\right)}{\delta }\right]}^{2}\frac{\left(1+\text{c}\right)}{\text{c}},{\text{n}}_{2}=\text{c}{\text{n}}_{1}$$

Using the superiority test, $\mu_{1-\alpha }=1.64,\mu_{1-\beta }=1.28.\pi =0.8,c=1,\delta =0.15$, calculate n1 = n2 = 122. Considering the clinical dropout rate of about 10%, a total of 272 cases need to be included. The included patients will be numbered according to the order of visits, and will be divided into an experimental group and a control group using a completely random method, with 136 cases in each group.

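### As printed, the primary-endpoint categories do not fit an NYHA I to III population: the top category cannot be reached and a III-to-I improvement falls in none of the four

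*Protocol article*

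**What the plan says.** Section 2.6.1 (Efficacy indicators) makes the total effective rate the main efficacy measure, judged by NYHA class: "total effective rate = (marked effective number + effective number)/total number × 100", expressed as a percentage. It prints four categories:

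- "Marked effective: cardiac function improved by more than grade 2"
- "Effective: cardiac function improved by grade 1, but not as good as grade 2"
- "Ineffective: cardiac function improved less than grade 1"
- "Deterioration: the deterioration of heart function is less than grade 1"

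Section 2.3 (Patients) lists "Cardiac function grade I to III" as an inclusion criterion and "Cardiac function grade IV" as an exclusion criterion. Nothing else in the article restates or corrects the cut-offs. Section 2.6.1 refers to an external guideline for the rate, but the article prints its own definitions.

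**The concern.** NYHA class moves in whole steps, and the eligible range is only three classes wide. Cut-offs that demand more than two steps up, or less than one step down, may describe changes that no enrolled patient can show. If a real and favourable change also falls between two categories, the numerator of the primary endpoint is undefined for those patients.

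At stake is how III-to-I patients are scored. If Tai Chi works, such patients should be more common in the experimental arm, so leaving them out would shrink the observed difference. If the rule is instead settled during analysis, the primary endpoint is fixed by someone who may already have seen data.

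**Working it through.** **Inputs.** Baseline class I, II or III (section 2.3). Final class I to IV. The four category definitions and the rate formula (section 2.6.1). Rate 0.8, difference 0.15, quantiles 1.64 and 1.28, equal allocation and 10% dropout (section 2.4).

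**Step 1: the plan's own figure.** n per arm = π(1 − π) × [(1.64 + 1.28)/δ]² × (1 + c)/c = 0.8 × 0.2 × (2.92/0.15)² × 2 = 121.26, rounded up to 122. Allowing for dropout, 122/0.90 = 135.6, rounded up to 136 per arm, or 272 in total. The stated figures reproduce. They depend on an assumed rate and difference, not on the category wording.

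**Step 2: every possible change against the printed rules.** Improvement = baseline class minus final class. There are 3 × 4 = 12 transitions.

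| Transition | Improvement | Category as printed |
|---|---|---|
| III to I | 2 | none: not above 2, not below 2, not below 1 |
| II to I, III to II | 1 | effective |
| I to I, II to II, III to III | 0 | ineffective |
| I to II, II to III, III to IV | −1 | not deterioration; ineffective only if a negative gain counts as a gain below 1 |
| I to III, II to IV | −2 | same |
| I to IV | −3 | same |

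- *Marked effective* needs a gain above 2. The maximum is 3 − 1 = 2, so 0 of 12 transitions qualify.
- *Deterioration* needs a loss above 0 but below 1 class. On a whole-class scale 0 of 12 qualify, and all six worsening transitions lie outside it.
- III to I is the only transition that fits no category under any arithmetic reading.

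**Step 3: effect on the total effective rate.** Let s be the class III share at baseline (equal across arms in expectation under randomisation), and let r_T and r_C be the proportions of class III patients who reach class I in the Tai Chi and control arms. Each arm's literal rate falls short of the rate of improvement by at least one class by s × r. The loss in the treatment difference is therefore

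loss = s × (r_T − r_C).

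The article gives none of these quantities. Assuming s from 10% to 50% and r_T − r_C from 0 to 20 points:

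| s | difference 0 | difference 10 points | difference 20 points |
|---|---|---|---|
| 10% | 0 | 0.10 × 10 = 1 point | 0.10 × 20 = 2 points |
| 30% | 0 | 3 points | 6 points |
| 50% | 0 | 5 points | 10 points |

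The planned difference is 15 points. If the top category is read as two classes or more, III-to-I patients are in the numerator and the loss is 0 throughout.

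**Step 4: the worsening cut-off.** A worsened patient is a non-responder whether called deteriorated, ineffective or left unlabelled, and the denominator is the total number. The rate does not change; only the four-way table does.

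**The case against.** The strongest reply is that the wording is a slip and that the text itself shows the intent. *Effective* is capped just below two classes, and the cap makes sense only if a two-class gain moves the patient up to *marked effective*. The categories form an ordered ladder and the numerator adds the top two rungs, so the natural meaning is improvement by at least one class. On that reading no responder is lost.

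This is plausible and should be accepted as the likely intent. It does not remove the defect. It needs the printed cut-off to be corrected, and the article nowhere does so.

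A reader might infer three stronger things that the documents do not support:

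- *That the trial will score its best responders as failures.* This follows only from the literal rule, and the article does not show how an assessor would handle a III-to-I patient.
- *That a definite part of the planned 15 points is lost.* With no baseline class mix and no III-to-I rates given, any single figure is one assumed scenario. Only a range starting at 0 is defensible.
- *That the faulty deterioration rule biases the primary rate.* It cannot, because worsened patients are non-responders either way.

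Nor does the cut-off error settle how deaths are classed or which visit is primary. Those are separate questions.

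**Conclusion.** The point holds as a definition error in a stated primary endpoint. Two of the four categories are empty for the eligible population, and the best possible outcome has no category. Only the III-to-I gap touches the total effective rate. Its effect on the treatment difference is 0 to 10 percentage points under the literal rule, assuming a class III share of 10% to 50% and a between-arm difference of 0 to 20 points in III-to-I rates. It is 0 under the likely intended reading. The existence of the gap rests on no assumption; its size rests entirely on these assumed ranges. The correction should be made before any outcome data are seen, because the choice of reading decides who counts as a responder.

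**What to change.** Reword section 2.6.1 in terms of change in NYHA class from baseline:

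- marked effective: improved by 2 or more classes;
- effective: improved by exactly 1 class;
- ineffective: no change;
- deterioration: worsened by 1 or more classes;
- total effective rate: proportion improved by at least 1 class.

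Each of the 12 transitions then falls in exactly one category. The cost is a few lines of wording. No extra data are needed, and the sample size stays at 122 per arm before dropout and 272 in total.

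One limit remains: patients who enter in class I still cannot improve, so they are non-responders under the new wording as under the printed one.
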